## Abstract

**Introduction::**

Hemorrhoidal disease is one of the most common and frequently occurring benign anorectal disorders, presented with bleeding and prolapsed, and surgery is the main and effective method for severe prolapsed hemorrhoids. Yet, the recurrence rate after procedure for prolapse and hemorrhoids (PPH) is significantly higher. To reduce the recurrence rate and protect the anus function, we try to carry out a randomized, controlled, prospective study to compare the efficacy and recurrence rate of tissue selecting technique (TST) with mega-window stapler (TST-MS) combined with anal canal epithelial preservation operation and PPH combined with external hemorrhoidectomy and inferior internal hemorrhoid ligation operation for the treatment of severe prolapsed hemorrhoids.

**Methods::**

This study is a single-center, evaluator-blinded, randomized, controlled clinical trial. Participants meet the inclusion and exclusion criteria in this RCT will be randomly divided into treatment group (TST-MS combined with anal canal epithelial preservation operation group) and control group (PPH combined with external hemorrhoidectomy and inferior internal hemorrhoid ligation operation) in a 1:1 ratio according to a computer-generated randomization list. The outcomes of recurrence, anal function, intraoperative variables, and postoperative complications will be recorded at different follow-ups.

**Conclusion::**

The findings of the study will help to explore the efficacy and recurrence rate of TST-MS combined with anal canal epithelial preservation operation on the treatment of severe prolapsed hemorrhoids.

**Trial registration::**

This study protocol was registered in open science framework (OSF). (Registration number: DOI 10.17605 / OSF.IO / 4JYNF).

## Introduction

1

Hemorrhoidal disease is one of the most common and frequently occurring benign anorectal disorders, presented with bleeding and prolapsed. The incidence is extremely high in adults according to different studies.^[1,2]^ In the treatment of hemorrhoids, surgery is still the main method for severe prolapsed hemorrhoids.^[3,4]^ The Milligan-Morgan hemorrhoidectomy (MMH) is the most effective and widely used treatment for symptomatic hemorrhoids of all the conventional hemorrhoidectomy (CH).^[5]^ By removing the hemorrhoid tissue with pathological changes, it could largely damage the anal cushion and the anal canal epithelium, associated with postoperative pain, and a 10% recurrence rate.^[6]^

Since first described by Longo in 1998,^[7]^ procedure for prolapse and hemorrhoids (PPH), also known as stapled hemorrhoidectomy, is an effective alternative by removing the prolapsed rectal mucosa on the dentate line to recover the anatomical position of internal hemorrhoids instead of just removing hemorrhoids. Several studies have shown it is an effective, safe, far less painful, and relative complication free procedure with fewer days off work.^[8–10]^ However, a large number of studies also show that the recurrence rate after PPH is 3.4% to 45%, which is significantly higher than the recurrence rate of conventional hemorrhoidectomy.^[8,11,12]^ Therefore, on the basis of the advantages of PPH technique, it is important to further reduce its postoperative recurrence rate.

Other than that the pathological changes of the hemorrhoids were not removed, the primary reason for the high recurrence after PPH is that for patients with third-grade hemorrhoids with severe internal rectal prolapse, the limited capacity of the PPH stapler cannot remove enough prolapsed tissue.^[13–16]^ At the same time, patients with severe prolapsed hemorrhoids are often accompanied by protruding external hemorrhoids, and approximately 12.7% of patients still suffer from residual external hemorrhoids after PPH stapler surgery.^[17]^ The combined method of PPH technique with the external hemorrhoidectomy and inferior internal hemorrhoid ligation^[18]^ could significantly reduce postoperative edema and residual external hemorrhoids, which expands the indications of PPH technique. However, there is still insufficient tissue removal for severely prolapsed hemorrhoids, which makes internal hemorrhoids prone to prolapse again. Also, external hemorrhoidectomy and inferior internal hemorrhoid ligation could partially damage the dentate line and the anal canal epithelium, which can easily cause stricture of anus and influence the anus function.

To reduce the recurrence rate and protect the anus function, we proposed a novel operation of tissue selecting technique (TST) with mega-window stapler (MS) combined with external hemorrhoid arc resection and suture to preserve the anal canal epithelium for the treatment of severe prolapsed hemorrhoids. The operation could make it better to treat internal hemorrhoids and hemorrhoid mucosa prolapse, reduce the incidence of internal hemorrhoids re-prolapse, completely excise the external hemorrhoids, preserve the anal cushion, dentate line, and anal epithelium, and protect the anal sensation and control bowel control. Therefore, we try to carry out a randomized, controlled, prospective study to compare the efficacy and recurrence rate of TST-MS combined with anal canal epithelial preservation operation and PPH combined with external hemorrhoidectomy and inferior internal hemorrhoid ligation operation for the treatment of severe prolapsed hemorrhoids.

## Method

2

### Study design

2.1

This study is a single-center, evaluator-blinded, randomized, controlled clinical trial (RCT). This trial has already been registered in open science framework (OSF) (Registration number: DOI 10.17605 / OSF.IO / 4JYNF). The protocol of the clinical trial has been approved by the Ethics Committee of Changshu Hospital of Traditional Chinese Medicine, and it will be carried out in accordance with the Declaration of Helsinki. The study protocol conforms to the Standard Protocol Recommendations for Interventional Trials (SPIRIT) 2013 Statement,^[19]^ and the results will be reported according to the CONSORT Statement extension for trials^[20]^ (Fig. 1).

**Figure 1 F1:**
[figure not shown]
Flow diagram of the study.

### Participants

2.2

#### Participants and sample size

2.2.1

Participants meet the inclusion and exclusion criteria in this RCT will be mainly recruited from inpatients of proctology department in Changshu Hospital of Traditional Chinese Medicine.

According to the previous report, the recurrence rate of PPH in the treatment of hemorrhoids was 9.6%. According to the preliminary experiment, the recurrence rate of severe prolapsed hemorrhoids by the TST-MS combined with anal canal epithelial preservation operation was 0%. Taking α = 0.05 and β = 0.2, 85 samples will be needed in each group. Considering the withdrawal rate of 20%, the total number of patients is determined as 204, that is 102 in each group.

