#### Randomization and blinding

2.2.4

The patients will be randomly divided into treatment group (TST-MS combined with anal canal epithelial preservation operation group) and control group (PPH combined with external hemorrhoidectomy and inferior internal hemorrhoid ligation operation) in a 1:1 ratio according to a computer-generated randomization list. Due to the limitation of treatment, the surgeons and patients are not blinded, and the statistical analysis will be carried out by an independent professional researcher who will not know the identification of the groups.

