### Statistical methods

2.5

Statistical analyses will be performed using the Statistical Package for the Social Sciences (SPSS) v22.0 software (SPSS Inc., Chicago, IL). Statistical testing is 2-sided and *P* < .05 is considered statistically significant. Efficacy outcomes are analyzed on an intent to-treat (ITT) basis who has at least 1 follow-up, and the last observation carried forward rule will be applied to manage missing data. Considering the homogeneity, group T test for normally distributed data or Mann–Whitney *U* test for non-normally distributed data will be used to compare variables between groups. For differences within each group, repeated measured analysis of variance will be used for assessments in different time points, whereas Wilcoxon signed-rank test will be selected for non-normally distributed data.

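### The 20% withdrawal allowance was multiplied on rather than divided out: 204 randomised leave about 81 per group with complete follow-up, not 85, and the 80% power needs a recurrence rate near 0% with the new operation

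*Protocol article*

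**What the plan says.** Section 2.2.1 (Participants and sample size) of the protocol article builds the sample size on recurrence. For the control side it says that "the recurrence rate of PPH in the treatment of hemorrhoids was 9.6" per cent. For the new operation it takes a preliminary experiment in which the rate with "TST-MS combined with anal canal epithelial preservation operation was 0" per cent. It continues: "Taking α = 0.05 and β = 0.2, 85 samples will be needed in each group". The last step is the withdrawal allowance: "Considering the withdrawal rate of 20%, the total number of patients is determined as 204, that is 102 in each group".

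Two other places bear on the check. Section 2.2.4 allocates patients "in a 1:1 ratio according to a computer-generated randomization list". Section 2.5 says "Statistical testing is 2-sided", and it analyses efficacy by intention to treat in patients with at least one follow-up, carrying the last observation forward. It names tests for continuous data but none for comparing proportions.

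**The concern.** An allowance for withdrawal should leave the required number after the losses have occurred. Withdrawals come out of the patients randomised, so the required number has to be divided by the fraction expected to stay. Adding 20% of the required number gives too few, and 102 is exactly 20% more than 85.

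The second strand is how much the 80% rests on the 0% assumed for the new operation. A small preliminary series with no recurrences is compatible with a low but non-zero rate. If power falls quickly as that rate leaves zero, a reader of a null result would credit the trial with more power than it had.

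**Working it through.** **Inputs.** All are from section 2.2.1 except the two-sidedness (2.5) and the 1:1 allocation (2.2.4): control recurrence 9.6%; new operation 0%; α = 0.05 two-sided; β = 0.2; 85 needed per group; 20% withdrawal; 102 per group, 204 in total.

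**Step 1: reproduce the plan's figure.** 85 × (1 + 0.20) = 102 per group and 2 × 102 = 204. This matches exactly.

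**Step 2: apply the plan's withdrawal rate to its own number.**
- Remaining per group: 102 × (1 − 0.20) = 81.6, so 81 to 82. Over both groups: 204 × 0.8 = 163.2, against 2 × 85 = 170.
- Number that would keep 85: 85 / (1 − 0.20) = 106.25, rounded up to 107 per group, 214 in total (10 more than 204).
- Withdrawal that 102 tolerates while leaving 85: 1 − 85/102 = 16.7%.

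**Step 3: power at the design point, 9.6% versus 0%, with 81 per group.** No test for proportions is named, so three are shown.
- Pooled z: Φ{(δ√n − 1.96·√(2p̄(1 − p̄))) / √(p₁(1 − p₁) + p₂(1 − p₂))}, with δ = 0.096 and p̄ = 0.048. This is Φ{(0.864 − 0.5925)/0.2946} = Φ(0.92) = 82%.
- Fisher's exact: with no events in the new arm, significance needs at least 6 recurrences in the control arm (6 v 0 gives p = 0.028; 5 v 0 gives p = 0.059). P(X ≥ 6) for X ~ Bin(81, 0.096) = 80.1%.
- Uncorrected chi-square: at least 4 recurrences are enough (4 v 0 gives 4.10, above 3.84; 3 v 0 gives 3.06). P(X ≥ 4) = 95.8%.

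With 85 per group Fisher gives 83.7%; with 80 it gives 79.2%. The shortfall therefore uses up the reserve under Fisher without crossing 80%.

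**Step 4: power when the new operation's rate is not zero.** Control 9.6%; Fisher and chi-square by enumerating all outcomes.

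| Analysed per group | True new-operation rate | Fisher | Pooled z | Chi-square |
|---|---|---|---|---|
| 81 | 0% | 80.1% | 82.2% | 95.8% |
| 81 | 1% | 58.6% | 68.9% | 73.3% |
| 81 | 2% | 41.3% | 54.4% | 54.1% |
| 85 | 0% | 83.7% | 84.0% | 96.8% |
| 85 | 1% | 62.2% | 71.0% | 75.5% |
| 85 | 2% | 44.3% | 56.4% | 56.6% |
| 102 | 0% | 93.4% | 90.0% | 99.1% |
| 102 | 1% | 74.7% | 78.7% | 83.8% |
| 102 | 2% | 55.9% | 64.3% | 66.5% |

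A 1% rate means less than one expected recurrence per group (81 × 0.01 = 0.81). The highest new-operation rate that keeps 80% power with 81 per group is 0% by Fisher, about 0.2% by pooled z and about 0.7% by uncorrected chi-square.

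**The case against.** The strongest objection is that the slip has no consequence at the design point: every test tried still gives at least 80% with 81 per group. That is correct. A reader might infer that the faulty allowance by itself leaves the trial underpowered, and the figures do not support that. What stands is that the protocol's own requirement of 85 is not met at its own withdrawal rate.

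Second, the efficacy analysis keeps anyone with at least one follow-up and carries the last observation forward, so some patients who withdraw would still be analysed. The analysed number could then lie anywhere between about 81 and 102 per group. This softens the shortfall but does not remove the error. Section 2.2.1 treats withdrawals as lost, since otherwise it would need no allowance, and about 81 remains the number with complete follow-up. With all 102 analysed, power at a 1% rate is 75% by Fisher and 84% by chi-square. At 2% both are below 80%.

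Third, a reader might infer that 80% power exists only if the new operation never recurs. That is true only for Fisher's exact test at 81 per group, and the protocol does not name that test. Uncorrected chi-square still gives 84% at a rate of 0.5%. Other pairs of rates also reach 80%. For example, an assumed 15% versus 2% gives 83% (Fisher) or 89% (chi-square) with 81 per group, and 15% lies inside the 3.4% to 45% that the Introduction reports for PPH. The supportable statement is narrower: at the 9.6% control rate the plan uses, power falls quickly once the new operation's rate reaches 1% or 2%.

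Last, a reader might infer that the 85 is itself wrong, because common formulas give other values (77 by two-sided pooled z, 97 with continuity correction). The article names no formula or software, and an article commonly leaves these, like the size of the preliminary experiment, to the full protocol. The 85 is taken here as given. The 9.6% and 0% are openly stated assumptions, not errors.

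**Conclusion.** The concern holds as an arithmetic error with a limited effect. The allowance was multiplied on, so 204 randomised give about 81 per group after 20% withdrawal, 3 to 4 fewer than the stated 85 (about 163 against 170 in total, or 4%). The true tolerance is 16.7%. Power at exactly 9.6% versus 0% stays at or above 80%.

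The larger practical point is sensitivity. With 81 analysed per group and 9.6% in the control arm, power is about 59% to 73% at a 1% rate with the new operation and 41% to 54% at 2%, depending on the test. These results assume independent binary outcomes, a two-sided 0.05 level and withdrawn patients counted as lost.

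**What to change.** Correct the paragraph in section 2.2.1 without enrolling more patients. Either of these would do:
- *204 patients will be randomised; at 20% withdrawal about 81 per group will be evaluable.*
- *102 per group allows for 16.7% withdrawal while retaining 85.*

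Then name the test that will be used for recurrence and give its power for the stated number at 9.6% in the control arm and 0%, 1% and 2% in the new-operation arm. The table under the working supplies these figures for Fisher's exact test and uncorrected chi-square at 81 and 85 per group.

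The cost is one paragraph, and the stated figures become slightly less favourable. Restoring the full 85 at 20% withdrawal would instead take 107 per group, 10 more patients in total. Power at the design point does not require that.

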#### Inclusion criteria

2.2.2

Patients are included if they meet the following inclusion criteria:

1.Patients meeting the diagnostic criteria for Circumferential mixed hemorrhoids, with internal hemorrhoids grade III–IV;2.Patients aged from 18 to 70 years’ old;3.Patients without obvious deformity of anus before the operation;4.Written informed consent.

#### Exclusion criteria

2.2.3

Patients are excluded if they present the following exclusion criteria:

1.Patients who have undergone mixed hemorrhoids surgery, or combined with other operations.2.Women in pregnancy, lactation, and menstruation.3.Patients with rectal cancer, rectal polyps, tuberculosis, Crohn disease, and other anorectal diseases.4.Patients with severe diseases of respiratory, digestive, circulatory, and blood systems, and obvious abnormal liver and kidney functions.5.Patients with acute inflammatory or thrombotic external hemorrhoids.

#### Randomization and blinding

2.2.4

The patients will be randomly divided into treatment group (TST-MS combined with anal canal epithelial preservation operation group) and control group (PPH combined with external hemorrhoidectomy and inferior internal hemorrhoid ligation operation) in a 1:1 ratio according to a computer-generated randomization list. Due to the limitation of treatment, the surgeons and patients are not blinded, and the statistical analysis will be carried out by an independent professional researcher who will not know the identification of the groups.

### Interventions

2.3

The preoperative and postoperative treatment of the 2 groups is the same. Before the operation, the patients will get blood routine test, urine routine test, liver and kidney function, blood glucose, coagulation, infectious disease indicators, electrocardiogram, chest x-ray examination, and abdominal ultrasound, colonoscopy, pathological biopsy, if necessary, to exclude surgical contraindications. The circumference of the anal canal will be measured before the operation. Intraspinal anesthesia will be used in all cases, and the left lateral decubitus will be taken during the operation. After the operation, the total amount of infusion in 6 hours is controlled within 500 mL to reduce the incidence of urinary retention, with 5 consecutive days of routine antibiotics.

#### Intervention group

2.3.1

1. Internal hemorrhoid surgery will be performed with TST-33-MS (Touchstone International Medical Science Co, Ltd, Suzhou, China) with the following procedure:

① Routinely disinfect the perineum area;② Appropriately expand the anus, insert an anoscope, and remove the inner tube to reveal the hemorrhoid tissue to be removed;③ Purse—string suture the hemorrhoid with “0” silk thread 3 to 5 cm from the dentate line only on the mucosa and submucosa;④ Unscrew the tail wing of the stapler counterclockwise, put the head of the stapler into the anal expander after the head and the body of the stapler are completely loosened, tighten the 2 ends of the purse string around the central rod, lead the suture string out from the symmetrical hole of the stapler through the string lead-out rod, tighten the stapler clockwise, and pull the drawn rectal tissue into the staple groove. At this time, when feel the resistance of the knob, fire the stapler to achieve the cutting and anastomosis. After waiting for 30 seconds, unscrew the tail 3/4 lap counterclockwise and take out the stapler;⑤ Observe the anastomosis, suture to stop the bleeding if there is active bleeding.

2. Surgery of external hemorrhoids will be performed with the operation of arc resection and suture to preserve the anal canal epithelium with the following procedure:

① After the successful anastomosis, carefully check the remaining external hemorrhoids outside the anus;② Clamp the 2 ends of the external hemorrhoids with a vascular clamp, and make an arc-shaped incision in the anal canal skin line with a dermatome; peel from the incision and trim the skin edge to smooth if there are severe varicose veins;③ Perform mattress suture using 3-0 absorbable thread as the skeleton of the incision, and 4-0 absorbable thread for both ends and the suture gap;④ Examine the resected specimens and submit for pathological examination.

#### Control group

2.3.2

PPH stapler will be performed for internal hemorrhoids with the same procedure with that in the treatment group; the external hemorrhoids will be stripped to the vicinity of dentate line and ligated at a low position.

### Outcome variables

2.4

Follow-up of visits to the hospital is required at week 2 and 4 after surgery, and telephone follow-ups are conducted at week 3, 8, and 1 year after the operation, to report and record the following variables (Table 1).

**Table 1 T1:** Outcome variables assessed during the study.

			Post-operation							Follow up			
				
	Preoperation	Intraoperation	12 h	Day 1	Day 2	Day 3	Day 5	Day 7	Wk 2	Wk 3	Wk 4	Wk 8	1 y
Primary outcomes													
Anal function													
Incontinence score	✓										✓		
Circumference of anal canal	✓										✓		
Recurrence										✓	✓	✓	✓
Secondary outcomes													
Operating time		✓											
Intraoperative blood loss		✓											
Weight and volume of excised specimen		✓											
Anal pain			✓	✓	✓	✓	✓						
Bleeding			✓	✓				✓	✓				
Urinary retention			✓	✓	✓	✓	✓	✓	✓				
Anal edge edema			✓	✓				✓	✓				

#### Primary outcomes

2.4.1

1.Anal function① Incontinence score:Wexner score will be used to evaluate the anal function of patients before and 4 weeks after the operation.② Circumference of the anal canalMeasure the circumference of the anal canal once before and 4 weeks after the operation.2.Recurrence of internal hemorrhoids and residual external hemorrhoids

Re-prolapse and obvious bleeding of internal hemorrhoids after the operation can be regarded as recurrence. Count the number of recurrences and residual recurrences of external hemorrhoids within 1 year after the operation.

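### Three (or four) outcomes are called primary under one undivided two-sided 0.05, only recurrence was used for the sample size, and no rule says whether any or all must succeed

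*Protocol article*

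**What the plan says.** - **Primary outcomes (protocol article, 2.4.1 and Table 1).** Two numbered items carry the label. The first, anal function, contains the Wexner score and the anal canal circumference, each taken before surgery and at week 4. The second is "Recurrence of internal hemorrhoids and residual external hemorrhoids", counted over the first postoperative year. Table 1 shows three primary rows, with a single row for recurrence.
- **Threshold (2.5).** One rule covers everything: "Statistical testing is 2-sided and *P* < .05 is considered statistically significant".
- **Sample size (2.2.1).** The only inputs are recurrence rates, 9.6% for PPH and 0% for the new operation: "Taking α = 0.05 and β = 0.2, 85 samples will be needed in each group". No effect size or standard deviation is given for the Wexner score or the circumference.
- **Success rule.** The article does not rank the primary outcomes, divide alpha between them, require all of them to succeed, or say which one decides the trial.

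**The concern.** Three choices made in the protocol do not fit together: several primary outcomes, one undivided alpha, and a sample size derived from one of them. As written, the text does not settle what a positive trial would be.

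Timing makes this matter. The two functional measures are complete at week 4, while recurrence runs to 1 year. A week-4 difference in circumference or Wexner score at P < .05 could be reported as a positive primary result whatever the 1-year recurrence count shows. The stated aim in the abstract and introduction is to compare efficacy and recurrence, and the patient numbers were justified by recurrence.

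**Working it through.** **1. Inputs.** Two-sided alpha 0.05 (2.5); beta 0.2, rates 9.6% and 0%, 85 per group, 20% withdrawal, 102 per group (2.2.1); 1:1 allocation (2.2.4); three primary outcomes, or four if the recurrence item is split (2.4.1, Table 1). Correlations between outcomes are not given. Values of 0.3 to 0.8 are my assumption.

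**2. The plan's own figure.** The two-sided pooled formula is

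n = [z(1−α/2)·√(2p̄q̄) + z(1−β)·√(p₁q₁ + p₂q₂)]² / (p₁ − p₂)²

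With p₁ = 0.096, p₂ = 0 and p̄ = 0.048, √(2 × 0.048 × 0.952) = 0.3023 and √(0.096 × 0.904) = 0.2946. Then n = (1.960 × 0.3023 + 0.8416 × 0.2946)² / 0.096² = 76.6, so 77. A continuity correction gives 97, and a Fisher exact power search gives 81. None of these is 85. The 102 is 85 × 1.2; dividing by 0.8 would give 107. These are separate matters and do not affect the present point. What matters here is that the calculation uses recurrence only, at the full 0.05.

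**3. False-positive chance if any one primary suffices.** With k independent tests at 0.05 it is 1 − 0.95^k:

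- k = 3: 1 − 0.8574 = 14.3%
- k = 4: 1 − 0.8145 = 18.5%

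With equally correlated normal test statistics (simulation, 400,000 draws):

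| Assumed correlation | Three outcomes | Four outcomes |
|---|---|---|
| 0.3 | 13.6% | 17.4% |
| 0.5 | 12.5% | 15.6% |
| 0.8 | 9.8% | 11.5% |

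**4. If all primaries must succeed.** The false-positive chance does not exceed 5%. Overall power is then at most the power of the weakest test. For the Wexner score and the circumference that power cannot be computed, because no effect size or standard deviation is stated.

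**5. Power for recurrence at 85 per group.** Power = Φ{[0.096·√85 − z(1−α/2) × 0.3023] / 0.2946}, with 0.096·√85 = 0.8851:

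- α = 0.05 (single primary, or first in a fixed sequence): (0.8851 − 1.960 × 0.3023) / 0.2946 = 0.993, power 84.0%
- α = 0.05/3 = 0.0167: (0.8851 − 2.394 × 0.3023) / 0.2946 = 0.548, power 70.8%
- α = 0.05/4 = 0.0125: (0.8851 − 2.498 × 0.3023) / 0.2946 = 0.441, power 67.0%

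The last two are Holm's strictest step. Holding 80% power there needs 103 or 110 evaluable patients per group.

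**The case against.** The strongest reply is that a journal article condenses a fuller protocol, and that multiplicity rules often sit in an analysis plan, which is not shown and might contain a hierarchy. That stands as far as it goes: the absence of a testing order would not by itself be a finding. But the primary labels, the common threshold and the basis of the sample size are all stated here, and they conflict as stated. The numbering in 2.4.1 does not resolve this. It reads as a list, and if taken as an order it would put the two outcomes without a power calculation ahead of the one that has it.

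Three stronger readings are tempting, and the document does not support them.

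- **That the familywise error is 14.3% or 18.5%.** A reader might infer this, but it holds only if any one positive primary counts as success, which the article neither states nor excludes. Both figures also assume independence, and the four-outcome count is the less favourable reading. Section 2.5 names no test for proportions. If recurrence were tested by Fisher's exact test at 85 per group, its actual size would be about 1.7% to 2.9% for a common rate of 4.8% to 9.6%. Three independent outcomes would then give about 11.3% to 12.4% (1 − 0.95² × 0.983 to 1 − 0.95² × 0.971).
- **That a week-4 claim of success is intended.** Nothing says so. The text merely leaves it open, while the stated aim and the sample size both point to recurrence.
- **That the trial was powered for internal-hemorrhoid recurrence at 1 year.** Section 2.2.1 attaches no time horizon to the 9.6% and does not restrict it to internal hemorrhoids.

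**Conclusion.** The point holds in conditional form. The protocol names three or four primary outcomes, applies one undivided two-sided 0.05 and sizes the trial on recurrence, without saying what combination of results makes the trial positive. Under the any-one reading, the chance of a false-positive primary result is about 10% to 14% for three outcomes and 11% to 18.5% for four, across assumed correlations from 0.8 down to independence. It would be somewhat lower if a conservative exact test is used for recurrence. Under the all-must-succeed reading, alpha is protected but the trial's overall power is not established. Either way the wording needs correcting before any results are known.

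**What to change.** In 2.4.1, Table 1 and 2.5:

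1. Name recurrence within 1 year, the type of outcome used for the sample size, as the single primary outcome at two-sided 0.05.
2. State whether it includes residual external hemorrhoids, so that it matches the outcome behind the 9.6%.
3. Make the Wexner score, the circumference and any separate residual-external-hemorrhoid outcome secondary. Test them at 0.05 in a fixed order chosen in advance by the investigators, each only while the preceding test is significant.

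**Cost.** Wording only. Alpha for recurrence stays at 0.05, so it loses no power and no patients are added for this reason. The downside is that confirmatory claims about anal function become conditional on a significant recurrence result.

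**Alternative, not preferred.** Keeping all outcomes primary with Holm's procedure also controls the error, but it is not free. At its strictest step, power for recurrence at 85 per group falls from about 84% to about 71% (three outcomes) or 67% (four). Restoring 80% needs 103 or 110 per group, which is 129 or 138 after dividing by 0.8 for withdrawal, against the planned 102.
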